## Trial design {8}

This study was designed as a multicenter, randomized, parallel, double-blind, placebo-controlled trial. Eligible participants will be randomly divided into two groups at a 1:1 ratio: *QZQG* group and placebo group. Randomly assigned numbers will be provided by a third-party research institution (School of Public Health, Fudan University, China). All enrolled patients will receive 1 day of screening, 7 days of intervention, and 21 days of observation.

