#### Inclusion criteria

*The inclusion criteria are as follows:*
Diagnosis of influenza A and/or B by a positive Rapid Influenza Diagnostic Test (RIDT) or reverse transcriptase-polymerase chain reaction (RT-PCR).• Positive results from local tests are acceptable if conducted within the 24 h prior to screening.• A patient with a negative RIDT may be enrolled if influenza is suspected based on local surveillance data or if the patient reports contact with a known case of influenza within the prior 7 days and all other inclusion criteria are met.Granting of written informed consent.Male or female aged 18 to 65 years at the time of signing informed consent form.Ability to comply with the study protocol, in the investigator’s judgment.Participants who require hospitalization for severe influenza or acquire influenza during hospitalization, the severity of which requires an extension of hospitalization.Participants will require at least one of the following objective criteria of severe influenza: (i) duration with axillary temperature over 39 °C ≥ 3 days, accompanied by severe cough, sputum, blood sputum, or chest pain; (ii) rapid respiratory rate (≥30 times per minute), difficulty breathing and cyanosis of lips; (iii) arterial oxygen saturation (SaO2)/ pulse oxygen saturation (SPO2) ≤94% in room air condition; (iv) requires ventilation or supplemental oxygen to support respiration; (v) with only one complication related to influenza (e.g., pneumonia, central nervous system involvement, myositis, rhabdomyolysis, acute exacerbation of chronic kidney disease, asthma or chronic obstructive pulmonary disease (COPD), severe dehydration, myocarditis, pericarditis, exacerbation of ischemic heart disease).The time interval between the onset of symptoms and randomization is within 96 h. The onset of symptoms is defined as either time of the first increase in body temperature (≥ 38 °C) or time when the patient experiences at least one general or respiratory symptom.Conforming to the standard of TCM syndrome differentiation.

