#### Secondary outcome measure

Secondary outcomes are the following:
Time to clinical improvement of symptoms (TTCIS) [time frame: baseline to day 14].Participants assessed the severity of 7 influenza-associated symptoms (cough, sore throat, headache, nasal congestion, feverishness/chills, muscle/joint pain, and fatigue) on a 4-point scale (0 = no symptoms, 1 = mild, 2 = moderate, and 3 = severe). TTCIS was defined as the time from the start of treatment to the time when all influenza symptoms were alleviated, as defined below, for a duration of at least 21.5 h:• Pre-existing symptoms (cough, fatigue, or muscle/joint pain that existed prior to influenza) that were worse at baseline must have improved at least 1 point from baseline.• New symptoms must have alleviated, defined as a symptom score of none (0) or mild (1).Time to defervescence (TTD) [time frame: baseline to day 14].Time to defervescence includes defervescence onset time and the time to complete defervescence. Defervescence onset time is defined as the time from the start of treatment to the time when the body temperature decreases to ≤37.3 °C. And complete defervescence is defined as the time from the start of treatment to the time when the temperature of ≤37.3 °C sustained for ≥ 24 h [14, 28].Percentage of participants with 2 or more Influenza-related complications [time frame: baseline to day 28].Secondary influenza complications include pneumonia, encephalitis, meningitis, encephalopathy, myelitis, Guillain-Barré syndrome, myocarditis, pericarditis, myositis, and septic shock.Percentage of participants whose symptoms were improved at each time point [time frame: 12, 24, 36, 48, 72, 96, 120, 144, and 168 h after the initial dose of study treatment]. The criteria for improvement of influenza symptoms have been described above.Percentage of participants reporting normal temperature at each time point [time frame: 12, 24, 36, 48, 72, 96, 120, 144, and 168 h after the initial dose of study treatment]. Defined as the percentage of participants whose axillary body temperature dropped to equal or less than 37.3 °C after the initiation of the study treatment.Body temperature at each time point [time frame: 12, 24, 36, 48, 72, 96, 120, 144, and 168 h after the initial dose of study treatment]. Participant’s self-measured axillary temperature using an electronic thermometer.Percentage of participants requiring systemic antibiotics for infections secondary to influenza [time frame: day 2 to day 28].Percentage of participants with adverse events (AEs).Inpatient length of stay defined as number of days in hospital [time frame: day 2 to day 28].Median time (days) receipt of oxygen [time frame: day 2 to day 28].

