## Assignment of interventions: allocation

### Sequence generation{16a}, concealment {16b}, and implementation {16c}

According to a stratified block randomization method, all patients are stratified by study center and randomly assigned to the *QZQG* group and placebo group in a 1:1 ratio. The random sequence and the randomization list of every center will be generated by the independent specialist from School of Public Health, Fudan University, China using the PRCO PLAN function of the analysis system of SAS software (SAS, Cary, NC, USA). The randomization sequence will be concealed in a lightproof sealed envelope for emergency unblinding events, which will be kept by the independent specialist and the Sponsor. An independent drug administrator at every center will assign numbered packs of study drugs to eligible patients in order by randomization list.

An emergency letter including the random sequence and assignment has been prepared in all of centers. In any emergency medical situation, such as serious adverse event or deteriorative condition, the unblinding process will be started after contacting the Sponsor and the primary investigator. The investigators from Longhua Hospital Affiliated to Shanghai University of traditional Chinese Medicine will record the details of urgent unblinding and make sure the corresponding patient is excluded. If the rate of drug blinding leakage or emergency letter opening rises more than 20%, this trial will be considered as failure.

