### Methods for any additional analyses {20b}

Subgroup analysis of all endpoints will be conducted based on chronic respiratory diseases (with or without), complications (with or without) and course of disease (< 3 days and ≥ 3 days). Subgroup analyses will be produced where appropriate and where the number of patients in each subgroup is sufficient.

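### The two-or-more complications outcome does not exclude complications present at entry, so patients need one or two new events depending on how they entered

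*Protocol article*

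**What the plan says.** Under Secondary outcome measure, the protocol article defines the outcome as "Percentage of participants with 2 or more Influenza-related complications [time frame: baseline to day 28"]. The sentence that follows names what counts: "Secondary influenza complications include pneumonia, encephalitis, meningitis, encephalopathy, myelitis, Guillain-Barré syndrome, myocarditis, pericarditis, myositis, and septic shock".

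Under Inclusion criteria, the severity routes are alternatives: "Participants will require at least one of the following objective criteria of severe influenza". Routes (i) to (iv) rest on fever with symptoms, respiratory rate with dyspnoea and cyanosis, oxygen saturation, and need for ventilation or oxygen. Route (v) is "with only one complication related to influenza (e.g., pneumonia, central nervous system involvement, myositis" and further examples, among them myocarditis and pericarditis. Pneumonia, myositis, myocarditis and pericarditis thus appear both as entry examples and as outcome conditions.

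Two further places bear on this. Methods for any additional analyses {20b} plans subgroups of all endpoints by "complications (with or without"), so a mixture of patients is expected. The section on sequence generation states that "all patients are stratified by study center and randomly assigned to the" two groups; complication at entry is not a stratification factor.

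**The concern.** An outcome meant to show what treatment prevented should start from the same place for every patient. Here the count opens at baseline, and some patients already have one of the two complications that it requires.

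Three things are at stake:

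- Complications that arose before randomisation, which treatment cannot have affected, supply part of the outcome.
- One new complication, even a serious one such as septic shock, does not register in a patient who entered with none.
- A chance difference between arms in the share entering with a complication passes into the outcome rates.

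The same section shows that the distinction was available. Antibiotic use, length of stay and oxygen receipt are timed from day 2, and the symptom outcome has separate rules for pre-existing and new symptoms. The complications outcome has no such rule.

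**Working it through.** **No figure to reproduce.** The protocol gives no rate, effect or power for this outcome. The point rests on comparing the two definitions; the numbers below only illustrate its consequence.

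**Step 1: the definitions side by side.** Entry by route (v) means exactly one complication. If it is on the outcome list, the count starts at 1 and the patient needs 2 − 1 = 1 new event. Entry by routes (i) to (iv) without a complication starts at 0, and the patient needs 2 − 0 = 2 new events.

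**Step 2: how far apart the two requirements are.** Assume that new complications follow a Poisson distribution with mean m per patient. Neither m nor the distribution is in the documents.

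- At least one new: P1 = 1 − e^(−m)
- At least two new: P2 = 1 − e^(−m) − m·e^(−m)

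For m = 0.2, e^(−0.2) = 0.8187, so P1 = 0.1813 and P2 = 1 − 0.8187 − 0.1637 = 0.0175.

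| m (assumed) | Enters with one listed complication (P1) | Enters with none (P2) | Ratio |
|---|---|---|---|
| 0.05 | 4.9% | 0.1% | about 40 |
| 0.1 | 9.5% | 0.5% | about 20 |
| 0.2 | 18.1% | 1.8% | about 10 |
| 0.3 | 25.9% | 3.7% | about 7 |
| 0.5 | 39.3% | 9.0% | about 4 |

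The patients who enter with none and have exactly one new event are the ones not counted: m·e^(−m), or 16.4% of them at m = 0.2.

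**Step 3: chance imbalance.** With share f entering with a complication, an arm's rate is f·P1 + (1 − f)·P2. With no treatment effect and m = 0.2:

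- f = 50%: 0.5 × 0.1813 + 0.5 × 0.0175 = 9.9%
- f = 60%: 0.6 × 0.1813 + 0.4 × 0.0175 = 11.6%

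A 10-point imbalance at entry moves the outcome by about 1.6 points. With 228 / 2 = 114 per arm and an assumed share of 50%, the standard error of the difference in shares is roughly √(2 × 0.25 / 114) = 6.6 points, so a 10-point imbalance is about 1.5 standard errors. The significance level of the usual test still holds; the cost is noise and harder interpretation.

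**Step 4: power, as illustration only.** Assume m = 0.3 on placebo, halved to 0.15 on treatment, f = 50%, 114 per arm, two-sided 5%, unpooled normal approximation.

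- As written: placebo 0.5 × 0.2592 + 0.5 × 0.0369 = 14.8%; treatment 0.5 × 0.1393 + 0.5 × 0.0102 = 7.5%. Standard error 0.0414, z = 0.0734 / 0.0414 = 1.77, power about 43%.
- At least one new complication: 25.9% against 13.9%. Standard error 0.0523, z = 0.1199 / 0.0523 = 2.29, power about 63%.
- At least two new complications for everyone: 3.7% against 1.0%, power about 27%.

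With m from 0.2 to 0.4, f from 30% to 70% and the halving kept, power is 23% to 62% as written and 48% to 74% for at least one new. With a 20% reduction (m = 0.3, f = 50%) the two are about 10% and 13%; with m = 0.05 halved they are about 11% and 16%.

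**The case against.** The strongest defence is that one rule applies to everyone: a total of two or more by day 28. That is a legitimate measure of complication burden, and two sits naturally above the ceiling in route (v), "with only one complication related to influenza". On this view, wanting new events is a preference between estimands. It stands in part, since burden is a coherent summary. It does not explain why events before randomisation should count towards a treatment outcome, or why progression should take two steps for patients who enter with none.

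A second defence is that only new events were intended and that the analysis plan will say so. The article fixes the threshold and the window, and neither carries that restriction. If it was intended, everyone would need two new events, and single new complications would be lost for all.

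A third is the planned subgroup analysis. If it refers to complications at entry, the distance to the threshold is largely uniform within each subgroup. That mitigates the problem, but the subgroups are conditional on sufficient numbers, and results across them would still be measured against different requirements.

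Some stronger readings should be resisted:

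- A reader might infer that the outcome mostly reflects entry status. A route (v) patient cannot meet it on that single entry complication and always needs a new one; at m = 0.3, 74% of such placebo patients would never meet it.
- A reader might infer that the arms are compared unfairly. Allocation is random at 1:1, so the mix is balanced in expectation.
- A reader might infer that the entry and outcome lists contradict each other, because rhabdomyolysis, asthma or COPD exacerbation and others are named only at entry. The entry list is given as examples and the outcome list as inclusions, so both can be read as open. This is an ambiguity about the starting count.

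Nor are serious single events lost to the trial: adverse events are recorded regardless of cause. They are lost only to this outcome.

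**Conclusion.** The point holds as a defect of definition in one secondary outcome. As written, complications present at entry are not excluded, so patients need one or two new events according to entry status, single new events in patients entering with none go uncounted, and chance imbalance in entry complications carries into the result. This rests on the text alone.

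Its size is not known. The 4-fold to 40-fold gap depends on an assumed Poisson mean of 0.05 to 0.5. The power figures depend further on an assumed effect, an assumed entry share and all 114 per arm being analysed, although 10–20% dropout is expected and efficacy is analysed in a modified intent-to-treat set. They should not be read as a power loss that the documents establish: under a small effect or a low rate, neither definition has useful power. The primary outcome and the sample size are untouched. The priority is low, but the correction is cheap.

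**What to change.** Before unblinding, redefine the outcome as at least one new influenza-related complication by day 28, counting only complications with onset after randomisation (or after first dose; choose one), with the same threshold for every patient. Use one common list to classify complications at baseline and at follow-up for this outcome. Keep the total of two or more as a supportive summary, analysed with adjustment for complication at entry, for example as a covariate in the logistic model or as a stratum in the Cochran-Mantel-Haenszel test. State that the planned complications subgroup means status at entry, if that is the intention.

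The cost is revised outcome wording, an agreed list, and an onset date and baseline status for each complication in the case report form. The downside is that a single mild new complication then counts as an event; the supportive summary keeps the burden of multiple complications visible.

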
### Participant timeline {13}

The participant timeline is shown in Table 2.

**Table 2 Tab2:** shows the timeline of participant assessments/interventions

Process	Screening stage	Intervention stage	Observation stage		
	Day 0	Day 1 to day 7	Day 14 ± 1	Day 21 ± 2	Day 28 ± 2
**Acquisition of basic medical history**					
▪ Symptoms and signs	**x**				
▪ Basic conditions	**x**				
▪ Informed consent	**x**				
▪ Inclusion and exclusion criteria	**x**				
**Efficacy and safety assessment**					
▪ Vital signs (heart rate, blood pressure, breathing rate and oxygen saturation)	**x**	**x**	**x**	**x**	**x**
▪ Electrocardiograph	**x**	a			**x**
▪ Chest radiograph	**x**	a			**x**
▪ Laboratory inspection	**x**	a			**x**
▪ Record adverse events	**x**	**x**	**x**	**x**	**x**
▪ Body temperature	**x**	**x** (Measured at 4, 8, 12, 16, 20 and 24 o'clock)	**x**	**x**	**x**
▪ Record influenza symptoms	**x**	**x**	**x**	**x**	**x**
▪ Use of antibiotics		**x**	**x**	**x**	**x**
**Interventions**					
▪ *QZQG* formula or placebo		**x**			
▪ Concomitant medications (record only)	**x**	**x**	**x**	**x**	**x**
**Other**					
▪ Distribute patient information diary card	✓				
▪ Compliance record		✓			
▪ Inspection results record	✓	✓	✓	✓	✓
▪ Complete original record in CRF					✓
▪ CRF reviews and data entry					✓

×, must implement; a, necessary to implement

### Sample size {14}

Sample size calculations are based on the primary endpoint (the proportion of clinical improvement within 7 days after randomization). At the 5% significance level, a total of 101 patients per group is required to achieve 90% power and to determine an increase of 20% in the proportion of clinical improvement between *QZQG* group and the placebo group, assuming that the clinical improvement rate within 7 days after randomization of the placebo group receiving oseltamivir plus routine symptomatic treatment is about 50%. With an estimated dropout rate of 10–20%, a total of 228 patients are planned to be enrolled. If the initial hypothesis is not rejected, subsequent comparison is considered exploratory, and no conclusion is made.

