## Statistical methods

### Statistical methods for analyzing primary and secondary outcomes {20a}

The primary study analysis will occur when the last patient has either withdrawn or completed day 28 visit, and will be based on cleaned data for all patients up to and including this point. The clinical data will be managed and analyzed by the independent statisticians from a third party (School of Public Health, Fudan University,) in accordance with the statistical analysis plan. Data management and analysis will use SAS V.9.4 (SAS Institute, Cary, NC, USA).

All statistical inferences will be determined using two-sided tests. *P* < 0.05 will be considered significant, and 95% confidence intervals will be used. Data will be described as the mean, standard deviation, and confidence intervals. If necessary, minimum, maximum, P25, P75, and median values will be provided. Paired measurement data will also show the differences between the mean and standard deviation. When using nonparametric methods, median and mean values will be provided. Count data will be described using the frequency distribution and corresponding proportion. Qualitative information will be described using the positive rate, the number of positive cases, and the denominator.

Baseline data analyses (in FAS and PPS) will include demographic indicators and primary and secondary outcomes before intervention. Measurement data will be described using a *t*-test or *t*’ test (if the variance is absent). Count data will be described using the Pearson’s *χ*^2^ test. Rating data will be described using the two-sample Wilcoxon rank sum test.

Logistic regression model will be used to explore the efficacy (*QZQG* group and placebo group) and factors affecting efficacy. Dependent variable is the proportion of clinical improvement at day 7. In addition to drugs, independent variables also include the basic information and life behavior factors of participants. The basic information includes gender, height, weight, age, and underlying diseases that include chronic obstructive pulmonary disease, asthma, diabetes, hypertension, hyperlipidemia, hyperuricemia, cardiovascular disease, autonomic nervous dysfunction, lung cancer, other tumors, etc. Life behavior factors mainly include smoking and drinking.

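### The 101 per group matches a one-sided 5% calculation, but the plan tests two-sided: power is about 83% at 101 per group, not 90%, and 228 enrolled covers losses only up to 11.4% of the stated 10–20%

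*Protocol article*

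**What the plan says.** All design inputs are in the protocol article under Sample size {14}:

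- Level: "At the 5% significance level". Whether this is one- or two-sided is not given there.
- Control rate: "the placebo group receiving oseltamivir plus routine symptomatic treatment is about 50"%.
- Effect: "an increase of 20% in the proportion of clinical improvement between" the groups, read here as 50% versus 70%.
- Result: "a total of 101 patients per group is required to achieve 90% power".
- Enrolment: after allowing for an estimated dropout of 10–20%, "a total of 228 patients are planned to be enrolled".

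Trial design {8} fixes equal allocation: "Eligible participants will be randomly divided into two groups at a 1:1 ratio". Sidedness is settled under Statistical methods for analyzing primary and secondary outcomes {20a}: "All statistical inferences will be determined using two-sided tests", with P < 0.05 as the threshold. The same part of the article assigns Pearson's chi-square test to qualitative outcomes.

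Two further places affect how many patients reach the efficacy analysis. Under Inclusion criteria, "A patient with a negative RIDT may be enrolled if influenza is suspected" on local surveillance data or contact history. The analysis population section {20c} restricts efficacy analyses to an mITT set that is RT-PCR positive on central testing.

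**The concern.** The sample size and the planned test appear to rest on different error rates. A 50% versus 70% comparison with 90% power usually needs about 120 to 135 per group at two-sided 5%, so 101 looks too small. The enrolment total also looks too small for the upper part of its own dropout range.

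The stakes are high because the sample size section says that, if the initial hypothesis is not rejected, later comparisons are exploratory and support no conclusion. The confirmatory inference therefore rests on this one test. A reader of a null result would take the chance of having missed a true 20-point benefit to be 10%, when it is roughly 13% to 21% depending on loss.

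**Working it through.** **Inputs.** p₁ = 0.50, p₂ = 0.70, difference 0.20, mean 0.60, 1:1 allocation, 90% power. Normal quantiles: 1.645 (one-sided 5%), 1.960 (two-sided 5%), 1.282 (90% power).

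**Step 1: reproduce the plan's figure.** Pooled formula:

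n = [z_α √(2 × 0.6 × 0.4) + z_β √(0.5 × 0.5 + 0.7 × 0.3)]² / 0.20² = [0.6928 z_α + 0.6782 z_β]² / 0.04

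- One-sided 5%: (1.1396 + 0.8692)² / 0.04 = 100.9, rounded up to **101**. This is the stated figure.
- Two-sided 5%: (1.3579 + 0.8692)² / 0.04 = 124.0, so **124**.

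**Step 2: try other formulas and readings.**

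| Calculation at 90% power | One-sided 5% | Two-sided 5% |
|---|---|---|
| Unpooled variance | 99 | 121 |
| Pooled, as in step 1 | 101 | 124 |
| Arcsine | 102 | 125 |
| Pooled variance in both terms | 103 | 127 |
| Continuity-corrected | 111 | 134 |

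No two-sided variant comes near 101. Reading the 20% increase as relative (50% versus 60%) needs 423 per group one-sided or 519 two-sided. A two-sided continuity-corrected calculation at 80% power gives 103, which is neither 101 nor consistent with the stated 90%.

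**Step 3: power of the planned two-sided test.**

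Power = Φ{[0.20 √n − 1.960 × 0.6928] / 0.6782}

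For n = 101: (2.0100 − 1.3579) / 0.6782 = 0.961, and Φ(0.961) = 83.2%.

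| Evaluable per group | Situation | Normal approximation | Exact binomial, chi-square test |
|---|---|---|---|
| 114 | all 228 analysed | 87.4% | 87.5% |
| 101 | the plan's own target | 83.2% | 83.8% |
| 91 | 20% loss | 79.1% | 79.4% |

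**Step 4: the dropout allowance.** The plan needs 2 × 101 = 202 evaluable. The largest loss that 228 can absorb is 1 − 202/228 = 11.4%.

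| Loss | Left from 228 | Enrolment needed to keep 202 |
|---|---|---|
| 10% | 205 | 202/0.90 = 224.4, so 225 |
| 15% | 193 | 202/0.85 = 237.6, so 238 |
| 20% | 182 | 202/0.80 = 252.5, so 253 |

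Even the common shortcut of multiplying by 1 + loss gives 202 × 1.20 = 242.4, so 243 at 20%.

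**Step 5: PCR-negative exclusions, by assumption only.** The documents give no PCR-negative proportion. If 20% are lost and a further 5%, 10% or 20% of the remainder are PCR-negative, the numbers per group are 91.2 × 0.95 = 86.6, 91.2 × 0.90 = 82.1 and 91.2 × 0.80 = 73.0. The step 3 formula then gives about 77%, 75% and 70% power. The conclusion does not depend on this step.

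**The case against.** Several points can fairly be made for the plan.

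- **Sidedness is not stated beside the sample size.** That a one-sided formula was used is inferred from an exact numerical match. This is correct, but it does not help: either the 5% was two-sided and 101 is wrong, or it was one-sided and conflicts with the methods section. Nothing in the article declares or justifies a one-sided primary test.
- **The dropout allowance is not wholly wrong.** Enrolling 228 does cover 10% loss, which needs 225. This stands. The failure is above 11.4%, which is most of the stated range.
- **83% is one point in a range, and dropout need not remove a patient.** The mITT set is not defined by completion, and multiple imputation is planned for missing data. This also stands, although imputation does not fully restore lost information. Even with all 228 analysed, power is 87%.
- **The PCR point is uncertain.** The article does not define dropout, so PCR-negative exclusions may already be inside the 10–20%. A patient with a negative rapid test may also be PCR-positive. This stands, and it is why step 5 is only an illustration. What remains is that patients excluded by definition cannot be recovered by imputation, and the article does not say whether they were allowed for.
- **The test itself remains valid.** Type I error and the effect estimate are not affected. The error lies in the advertised power.

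**Conclusion.** The concern holds. On the article's own inputs, 101 per group gives 90% power only with a one-sided 5% test, whereas all inference is declared two-sided. The two-sided requirement is 124 per group. Power of the planned test is about 83% at 101 per group (84% exact), with a range from 87% with no loss to 79% at 20% loss, so 90% is not attained anywhere within 228. At 20% loss the chance of missing a true 20-point effect is about 21%, twice the stated 10%.

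Independently of sidedness, 228 supports 202 evaluable patients only up to 11.4% loss.

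These results assume an absolute 20-point increase from 50%, equal groups and an unadjusted two-proportion comparison, which is the calculation that reproduces 101. The power figures at each loss level also assume that lost patients contribute nothing to the analysis. The headline design figure is wrong as written and must be corrected.

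**What to change.** In Sample size {14}, state that the 5% level is two-sided and replace the power claim along these lines: 228 randomized gives about 83% power (two-sided 5%, 50% versus 70%) with 202 evaluable mITT patients, that is 11% loss, and 79% with 182, that is 20% loss. Replace the 10–20% allowance with the loss that 228 actually covers, and say whether patients excluded for negative central RT-PCR are counted in it. Drop the 90% figure for 101 per group. It could be kept only by openly declaring a one-sided 5% test, which would contradict the statistical methods section.

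This is a text correction with no change to design or conduct. Its cost is a less favourable stated power.

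If 90% power with the two-sided test is to be kept, 2 × 124 = 248 evaluable patients are needed: 248/0.90 = 275.6, so 276 enrolled at 10% loss, and 248/0.80 = 310 at 20%. That is 48 to 82 more patients than planned, so it is a change to the trial and not a wording correction.

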### Definition of analysis population relating to protocol nonadherence {20c}

The intent-to-treat (ITT) population is defined as all randomized patients, whether or not the patient received the assigned treatment. The ITT patients will be analyzed according to the treatment assigned at randomization. The ITT population includes the patients who agree to enroll in the study and sign an informed consent form. However, ITT population involves those who have never received study drugs or never completed observation records. Efficacy analyses will be conducted for the modified intent-to-treat (mITT) population. This is defined as all patients randomized who received at least one dose of *QZQG* formula and were centrally assessed as RT-PCR positive for influenza at any timepoint, with patients grouped according to the treatment assigned at randomization. The per-protocol set is used to analyze the main outcome for evaluating efficacy and to examine the consistency of the results from the mITT. The PPS is defined as follows: (1) full compliance with inclusion and exclusion criteria; (2) the compliance of medication consumption is over 80%; (3) the patients complete the test and record of the outcome and safety evaluation at every time node; and (4) completion of the clinical trial without major protocol violation. The safety analysis set (SAS) is defined as patients who received any amount of study treatment. Patients will be analyzed according to the treatment received. Patients who were randomized to the study but who did not receive any study drug will not be included in the safety population. The SAS will be used for the analysis of all safety indicators. Multiple imputation will be used for missing data.

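### The step from 202 to 228 patients allows for dropout only, although the efficacy set also removes centrally PCR-negative patients; the power for that set should be restated

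*Protocol article*

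**What the plan says.** **Sample size {14}.** "At the 5% significance level, a total of 101 patients per group is required to achieve 90% power". The design is a placebo improvement rate of about 50% and an increase of 20 points, with 1:1 allocation. The total follows from dropout alone: "With an estimated dropout rate of 10–20%, a total of 228 patients are planned to be enrolled".

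**Definition of analysis population {20c}.** Efficacy is assigned to the mITT. Besides a dosing condition, membership requires that patients "were centrally assessed as RT-PCR positive for influenza at any timepoint". Missing data are to be multiply imputed.

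**Inclusion criteria.** A positive rapid test is enough without PCR. In addition, "A patient with a negative RIDT may be enrolled if influenza is suspected based on local surveillance data"; reported contact with a known case in the previous 7 days also serves, provided the other criteria are met.

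**Statistical methods {20a}.** "All statistical inferences will be determined using two-sided tests".

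**The concern.** The entry rule, the analysis set and the sample-size arithmetic do not fit together. The entry rule admits patients whose influenza has not been confirmed by PCR. The analysis set removes those whom the central laboratory never finds positive. The sample-size section counts only dropout between enrolment and analysis. A PCR-negative patient can take all study drug and attend day 28, so is not a dropout in the ordinary sense.

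The stated 90% power therefore belongs to all randomised patients minus dropouts, which is not the set used for efficacy. This matters for reading a null result. Sample size {14} treats later comparisons as exploratory if the primary hypothesis is not rejected, so much rests on the primary test. A non-significant result would be judged against a power that was never worked out for the population analysed.

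**Working it through.** **Inputs.** From Sample size {14}: 50% versus 70%, 5% level, 90% power, 101 per group, 228 in total, dropout 10–20%. From Trial design {8}: 1:1 allocation, so 114 per group. The PCR-negative share *q* is not in the document; 5, 10 and 20% are assumed. The 50% and 70% rates are taken to apply to the mITT. The dosing condition in {20c}, which names only the active formula, is read as study drug in either arm.

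**Reproducing 101.** Pooled normal formula, mean rate 0.60:

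n = [z_α √(2 × 0.60 × 0.40) + z_β √(0.50 × 0.50 + 0.70 × 0.30)]² / 0.20²

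- One-sided 5%: [1.645 × 0.6928 + 1.2816 × 0.6782]² / 0.04 = 100.9, so 101. This is the printed figure.
- Two-sided 5%: 124. At 101 per group, two-sided power is 83.2%.

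The one-sided basis is used below only because it reproduces the plan's figure and so isolates the PCR effect.

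**How much loss 228 can absorb.** 1 − 202/228 = 11.4% from all causes. With *d* the proportion who lose the day-7 endpoint through dropout, the evaluable number is 228 × (1 − d) × (1 − q).

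- d = 10%: 228 × 0.90 = 205.2, and 1 − 202/205.2 = 1.6%. About 1.6% PCR-negative exhausts the margin.
- d = 0: the whole 11.4% is available for PCR exclusion.

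**Power.** Φ{[0.20 √n − z_α × 0.6928] / 0.6782}, with n = 114 × (1 − d) × (1 − q) per group, one-sided 5%:

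| PCR-negative (assumed) | n per group, d = 10% | Power | n per group, d = 0 | Power |
|---|---|---|---|---|
| 0% | 102.6 | 90.4% | 114.0 | 92.9% |
| 5% | 97.5 | 89.1% | 108.3 | 91.8% |
| 10% | 92.3 | 87.6% | 102.6 | 90.4% |
| 20% | 82.1 | 83.9% | 91.2 | 87.2% |

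The loss due to PCR exclusion alone is 1.3, 2.8 and 6.5 points at d = 10%, and 1.1, 2.5 and 5.7 points at d = 0.

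**Same shares under the two-sided test of {20a}.** For q = 0, 5, 10 and 20%: at d = 10%, 83.8, 81.8, 79.7 and 74.8%; at d = 0, 87.4, 85.7, 83.8 and 79.2%. The q = 0 values are already below 90%, so that part of the gap is not due to PCR exclusion.

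**The case against.** A reader might infer that the trial will certainly miss its evaluable number and its 90% power. The document does not support that, for four reasons.

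- **The PCR-negative share is unknown and may be small.** Ordinary entry needs a positive rapid test or PCR. The rapid-test-negative route is permissive and requires every other criterion, including onset within 96 h and the full TCM symptom pattern. One central positive at any time is enough for the mITT, and upper-tract, lower-tract and faecal specimens are listed for the central laboratory. Nothing in the text points to a share as high as 20%.
- **The 1.6% margin is a worst case.** It assumes that every dropout loses the primary endpoint. That endpoint is reached within 7 days in inpatients dosed under nurse supervision, while follow-up runs to day 28, so loss by day 7 may be well below overall dropout. Dosed, PCR-positive dropouts also stay in the mITT under multiple imputation. Imputation does not restore lost information, however, and does not apply to patients excluded by definition.
- **The lowest power figures belong mainly to other problems.** With no PCR-negatives at all, the two-sided test gives 83.8% at 10% dropout, and 20% dropout gives 87.2% one-sided. Those gaps come from sidedness and from the size of the dropout allowance.
- **Dropout is not defined in {14}.** It might be meant to cover every non-evaluable patient. Even so, 228 covers only 11.4%, near the bottom of the stated 10–20%, and the text does not say that PCR exclusions are included.

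The first three limit the size of the point. None removes it: the three sections still describe a source of loss that the calculation does not mention.

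**Conclusion.** The point holds as a conditional one. The plan's 90% power is worked out for a set other than its efficacy set, and 101 per group is missed once dropout and PCR exclusion together remove more than 11.4% of the 228. Whether that happens depends on a share that the document does not give and on how many dropouts lose the day-7 endpoint. The one-sided loss attributable to PCR exclusion is about 1 to 3 points at a share of 5–10% and about 6 points at 20%. It is worth correcting because it is cheap and affects how a null result is read; it does not show that the trial is badly underpowered.

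**What to change.** In Sample size {14}, state an assumed PCR-negative share with its basis, and give the evaluable number for the mITT as 228 × (1 − dropout) × (1 − PCR-negative share). Restate the power at 228 enrolled with the two-sided test of {20a}, preferably as a short table over a few shares, and say whether dropout means loss of the day-7 endpoint. A mid-trial update of the stated power is not needed, since it would change no decision.

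The cost is a sentence or two, a small table and a less favourable power figure. Enrolment, eligibility and the analysis set stay as they are.
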